**Figure 1 F1:**
[figure not shown]
Study Flowchart: Clinical Features, Management, and Outcomes of Neonatal Stroke.

**Figure 2 F2:**
[figure not shown]
Schematic of the multi-phase neonatal stroke research program infrastructure.

### Study participants

2.3

#### Inclusion criteria

2.3.1

Participants must meet all the following criteria:
Gestational age ≥28 weeks and ≤28 days postnatal, with identified stroke risk factors. (Extremely preterm infants <28 weeks are excluded by design due to diagnostic challenges and different pathophysiology.Clinical presentation of acute encephalopathy or seizures.Neuroimaging confirmation (MRI) of stroke (arterial ischemic, hemorrhagic, or cerebral venous sinus thrombosis), excluding other common etiologies. Clinically silent infarctions (incidental findings on imaging without clinical symptoms) will be excluded. To ensure complete case ascertainment, all neonates with identified risk factors for stroke (e.g., congenital heart disease, extracorporeal membrane oxygenation, or severe perinatal asphyxia) will undergo systematic screening with cranial MRI, and any asymptomatic infarctions detected will be documented separately but excluded from the primary analysis cohort**.**Parental or legal guardian consent.

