Prognostication of motor outcome following neonatal stroke has been an active area of research. Magnetic resonance imaging (MRI) assessment of the posterior limb of the internal capsule (PLIC) has been shown to correlate with the development of hemiparesis (11, 12). Quantitative scoring systems such as the Modified Pediatric ASPECTS have also been developed to correlate infarct volume with clinical outcomes (13). Additionally, the Hammersmith Infant Neurological Examination (HINE) and general movements evaluation are validated tools for early prediction of cerebral palsy (12). We acknowledge that this registry enrols only diagnosed cases; therefore, cumulative incidence will be calculated using total live births from all 22 participating hospitals as the denominator. However, this represents a hospital-based cohort rather than true population-based surveillance, and referral patterns may bias incidence estimates.

Shenzhen is particularly suitable as a model region due to its annual birth rate of approximately 200,000 live births, >98% NICU coverage across all districts, universal availability of cranial MRI and video-EEG at all participating hospitals, and the fact that >95% of regional births occur within the 22 study hospitals.

Therefore, establishing a prospective, multicenter cohort and dedicated registry is an urgent and foundational step. Such a resource is essential for accurately defining the disease burden, identifying associations with prenatal and perinatal factors that may inform future interventional studies, and mapping the evolution of neurodevelopmental outcomes from infancy through early childhood. By capturing comprehensive, longitudinal data within a real-world clinical setting, a registry can bridge the critical evidence gap between isolated clinical observations and population-level understanding.

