#### Secondary objectives

2.1.2

To characterize the clinical presentation, short-term treatment efficacy, and safety of the three subtypes of neonatal stroke: arterial ischemic stroke, cerebral sinovenous thrombosis, and hemorrhagic stroke.To identify significant prenatal, perinatal, and postnatal risk factors for neonatal stroke, and to develop and validate predictive models for risk stratification using a panel of early biochemical and imaging biomarkers.To analyze regional and institutional variations in the diagnostic, therapeutic, and rehabilitative management of neonatal stroke, and to propose evidence-based strategies for optimizing care and standardizing treatment protocols.

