#### Primary outcomes

2.5.1

Registry-based incidence of neonatal strokes in Shenzhen.

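### Section 2.3.1 makes an identified risk factor a condition of entry, so strokes without one drop out of the primary incidence numerator while all live births stay in the denominator

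*Protocol article*

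**What the plan says.** - **Eligibility (2.3.1).** The list opens with "Participants must meet all the following criteria". Its first item is "Gestational age ≥28 weeks and ≤28 days postnatal, with identified stroke risk factors". The other items are clinical presentation, MRI confirmation and consent.
- **What counts as a risk factor (2.3.1).** The article gives no closed list. The only illustration comes in the screening sentence, which covers "all neonates with identified risk factors for stroke (e.g., congenital heart disease, extracorporeal membrane oxygenation, or severe perinatal asphyxia"; these three conditions are examples.
- **Primary outcome (2.5.1).** "Registry-based incidence of neonatal strokes in Shenzhen", with no restriction to infants with risk factors. The primary objective in 2.1.1 has none either.
- **Numerator and denominator (Introduction).** The authors write "We acknowledge that this registry enrols only diagnosed cases", and that "cumulative incidence will be calculated using total live births from all 22 participating hospitals as the denominator".
- **Risk-factor aim (2.1.2).** "To identify significant prenatal, perinatal, and postnatal risk factors for neonatal stroke". Section 2.5.2 lists the characterization of risk factors as a secondary outcome.
- **Cases kept outside the cohort (2.3.1).** Asymptomatic infarctions are documented separately. Nothing equivalent is stated for symptomatic strokes without a risk factor.

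**The concern.** The numerator and the denominator follow different rules. An infant without a recognised risk factor who has seizures and a confirmed infarct is a neonatal stroke by the definition in the Introduction. That infant's birth counts in the denominator, but the infant cannot be enrolled. The registry would then report the incidence of stroke with a risk factor under the name of neonatal stroke. Enrolling more infants does not remove a bias of this kind.

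The Introduction attributes the gap between two earlier Chinese estimates, 1 in 2,660 and 1 in 8,373, largely to case ascertainment and referral. A restriction on who may be counted adds a further ascertainment difference to the study meant to clarify that gap.

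The same clause affects the risk-factor aim, because cases are selected on the characteristic to be described. It also means that the prognostic model is developed without infants who lack a risk factor.

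**Working it through.** **The plan's own figures.** The article gives no expected incidence under its eligibility rules and no share of strokes without a risk factor. Its sample-size figure in 2.6 reproduces (300 × (1 − 0.10 − 0.20) = 210) but does not bear on this point.

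**Inputs.** From the Introduction: neonatal stroke at about 1 in 3,000 to 1 in 5,000 live births, about 200,000 births a year, and more than 95% of births in the study hospitals. From 2.2: a six-year study period and a target of 300. Assumed: f, the share of otherwise eligible strokes with no identified risk factor, taken at 5%, 20% and 50%.

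**Step 1: incidence.** The denominator does not change, so observed incidence = true incidence × (1 − f). A true 1 in D reads as 1 in D/(1 − f).

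| True incidence | f = 5% | f = 20% | f = 50% |
|---|---|---|---|
| 1 in 3,000 | 1 in 3,158 | 1 in 3,750 | 1 in 6,000 |
| 1 in 4,000 | 1 in 4,211 | 1 in 5,000 | 1 in 8,000 |
| 1 in 5,000 | 1 in 5,263 | 1 in 6,250 | 1 in 10,000 |

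**Step 2: comparison with random error.** Exact Poisson 95% limits around 300 cases are about −11% and +12%. The true count is the observed count divided by (1 − f). It passes the upper limit when 1/(1 − f) > 1.12, that is, when f > 1 − 1/1.12 = 0.107. Above roughly 11%, the bias is larger than the random error in that direction; below it, the bias is smaller.

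**Step 3: risk-factor prevalence.** Every enrolled case has at least one identified factor, so the proportion with any factor is 100% whatever the truth. For a factor that itself qualifies an infant for entry, no carrier is lost, so its prevalence p becomes p/(1 − f). With p = 40%, this gives 0.40/0.95 = 42% at f = 5% and 0.40/0.80 = 50% at f = 20%. Individual factors still vary among cases. A recorded variable that does not qualify an infant could move in either direction.

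**Step 4: recruitment.** If enrolment ran for the full six years, births would be 200,000 × 0.95 × 6 = 1,140,000. That gives 380 strokes at 1 in 3,000 and 228 at 1 in 5,000. At f = 20% these fall to 304 and 182, against a target of 300.

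**The case against.** **The term may be read broadly.** Section 2.3.1 gives only examples, and 2.4.3 and 2.4.4 list many family, maternal, delivery and neonatal conditions. On a generous reading almost every case would have some factor, f could be well below 10%, and the bias could lie inside the random error. This stands as a limit on the size. It does not rescue the clause. An undefined term lets 22 hospitals apply it differently, and a clause that excludes nobody can be deleted without loss.

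**The clause may be loose drafting.** The same item states an aim of complete case ascertainment, so the authors may not have meant to exclude these infants. That is possible, but the text makes the condition mandatory and no other part of the article relaxes it.

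**The numerator is inferred.** The article does not say outright that only infants meeting all of 2.3.1 are counted. The inference rests on the statement that the registry enrols diagnosed cases, and on the absence of any other described count. A fuller protocol might hold a screening log. If so, the fix is easier, but the stated entry rule still conflicts with the primary outcome.

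**Stronger readings the documents do not support.**
- A reader might infer that detection itself depends on exposure, because screening MRI is tied to risk factors. The Discussion says that early MRI and video-EEG are mandated for infants with postnatal seizures, and 2.3.1 excludes silent infarctions. What remains is at most encephalopathy without seizures.
- A reader might infer that the prognostic model cannot be used in infants without risk factors. Nothing in the article says that these factors change prognosis after a stroke. The selection limits transportability and shows no more than that.

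**Conclusion.** The plan is wrong as written. A mandatory risk-factor condition contradicts a primary outcome and a denominator that carry no such condition, and following it biases the incidence downward. Confidence is high for the contradiction and for the direction of the bias.

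The size is not known. It depends wholly on f, which the documents do not give, and on how each site reads an open-ended term. Over the assumed 5% to 50%, the incidence is understated by the same 5% to 50%. The conclusion also assumes that the numerator is the enrolled cases.

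For the risk-factor aim, the proportion with any factor carries no information, and the prevalence of qualifying factors is inflated by 1/(1 − f). The sampling limits that the article acknowledges, such as a hospital-based cohort, referral patterns, confounding and attrition, do not include this selection.

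**What to change.** 1. By protocol amendment, delete the risk-factor clause from the first inclusion criterion in 2.3.1 and leave the gestational-age and postnatal-age limits as they are.
2. Keep risk factors as recorded data only. The modules in 2.4.3 already capture family, perinatal and neonatal history, so this needs no new collection.
3. Recover, or at least count, symptomatic MRI-confirmed strokes already screened out for lack of a risk factor, so that they enter the incidence numerator.

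A field for the route of detection, and a sensitivity analysis restricted to symptom-triggered cases, are optional.

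The cost is an amendment across the 22 sites and a look back at screened infants, since enrolment was planned from January 2025. The change enlarges the eligible pool, which helps the target of 300. It is best made early, because cases turned away become harder to recover.

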## Introduction

1

Neonatal stroke, defined as an acute focal neurological injury secondary to arterial ischemic infarction, hemorrhagic stroke, or cerebral venous sinus thrombosis occurring between birth and 28 days of life, is a leading cause of permanent neurological disability in infants (1, 2). This cerebrovascular event results in lifelong sequelae such as cerebral palsy, epilepsy, and cognitive impairments, with an estimated incidence ranging from 1 in 1,100 to 1 in 4,000 live births for perinatal stroke; the incidence of strictly neonatal stroke is less well defined but is approximately 1 in 3,000 to 1 in 5,000 live births (3–5) Critically, mortality rates range from 4% to 10%, underscoring its Status as a primary pediatric health concern (6, 7). Despite its profound impact, evidence-based strategies for prevention, acute management, and long-term prognostication remain significantly underdeveloped, with no standardized, population-based surveillance and outcome-tracking systems in many regions.

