One of the major contributions of this study is its focus on long-term neurodevelopmental outcomes, addressing a significant knowledge gap in China. International research has shown that between 20% and 50% of pediatric stroke survivors develop long-term cognitive impairments, including language deficits, memory decline, intellectual disabilities, and attention deficits, with some chronic language impairments persisting into adolescence (18, 19). However, these data largely derive from pediatric stroke cohorts that include children beyond the neonatal period. The developmental trajectory and neuroplasticity profile of neonatal stroke differ substantially from later childhood stroke due to the unique vulnerability of the developing brain (e.g., impaired myelination, synaptic pruning abnormalities) and its greater potential for reorganization. Where possible, we will present neonatal-specific outcomes separately. This study represents the first prospective registry-based cohort of neonates with stroke in China, incorporating a biobank of biological samples, including stool and breast milk, and tracking patient outcomes up to 5 years of age. The comprehensive nature of this cohort, which includes detailed neurodevelopmental assessments, will significantly advance standardized management of neonatal stroke nationwide.

We acknowledge that neonatal stroke comprises biologically and prognostically heterogeneous subtypes (arterial ischemic, hemorrhagic, venous sinus thrombosis). Subtype-specific analyses are planned for all primary and secondary outcomes.

The prospective design of this study offers substantial clinical and societal benefits. It is expected to deepen the understanding of neonatal stroke, enhance the management of pregnant women with underlying risk factors, and provide tailored guidance for delivery planning. Furthermore, the protocol mandates early cranial MRI and video EEG testing for infants presenting with postnatal seizures, ensuring prompt and accurate diagnosis. These measures are crucial for the early identification and management of neonatal stroke, facilitating timely interventions and better prognostic outcomes.

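### The primary outcome is named as the incidence of neonatal stroke, but eligibility admits only strokes presenting with acute encephalopathy or seizures, so infants with other signs go uncounted

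*Protocol article*

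**What the plan says.** All places are in the Protocol article.

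- **2.3.1 Inclusion criteria.** The criteria are joined: "Participants must meet all the following criteria". One of them is "Clinical presentation of acute encephalopathy or seizures". No other sign is listed as qualifying.
- **2.3.1, silent cases.** "Clinically silent infarctions (incidental findings on imaging without clinical symptoms) will be excluded". Where screening of at-risk infants finds them, "any asymptomatic infarctions detected will be documented separately but excluded from the primary analysis cohort".
- **1 Introduction, definition.** Neonatal stroke is "defined as an acute focal neurological injury secondary to arterial ischemic infarction, hemorrhagic stroke, or cerebral venous sinus thrombosis occurring between birth and 28 days". No presenting sign is required.
- **2.4.4 Standardized diagnostic and outcome criteria.** The three subtypes are defined without a presenting sign.
- **2.5.1 Primary outcomes.** The single entry is "Registry-based incidence of neonatal strokes in Shenzhen".
- **1 Introduction, denominator.** The registry enrols diagnosed cases only, and cumulative incidence is to be taken over total live births at all 22 hospitals. The caveat given there covers the hospital base and referral patterns.
- **3 Discussion, limitations.** Presentation is not mentioned.

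**The concern.** The numerator is restricted by how the infant presented. The name of the outcome, the definition of the disease and the denominator are not. The document gives a reason for leaving out infants below 28 weeks but none for the presentation criterion, and it does not tell the reader that the criterion limits what the incidence means.

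The effect falls on the only outcome listed as primary, and its direction is known: leaving out cases while keeping every birth in the denominator can only lower the rate. The Introduction attributes the spread between earlier Chinese rates largely to case ascertainment, and one aim of the registry is accurate epidemiological data. A filter on presentation is itself an ascertainment rule, so it should be visible in the outcome's name or removed from the numerator. Cases that are never logged during enrolment are hard to recover afterwards.

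**Working it through.** **Step 1. Where each type of case goes under the plan as written**

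| Infant with an MRI-confirmed neonatal stroke, other criteria met | Meets 2.3.1? | In the separate record of asymptomatic infarctions? |
|---|---|---|
| Acute encephalopathy or seizures | Yes | Not applicable |
| No clinical symptoms, found on imaging | No | Yes, if an infarction |
| Symptoms other than encephalopathy or seizures | No | No, because the infant is not asymptomatic |

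Section 2.4.1 prospectively identifies only neonates who meet the inclusion criteria, and the document describes no other route for the third row. That the numerator is the enrolled cases is inferred from the Introduction's statement about diagnosed cases and live births.

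**Step 2. The plan's own figures**

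The plan gives no figure for the expected incidence count or its precision. The sample-size figures in 2.6 reproduce: 300 × (1 − 0.10 − 0.20) = 210 evaluable, and 0.30 × 210 = 63 events, inside the stated 60–80. They serve the prediction model and do not bear on this point.

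**Step 3. Size of the shortfall**

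Inputs from the document:
- about 200,000 live births a year, and more than 95% of births in the 22 hospitals (Introduction);
- six years, January 2025 to December 2030 (2.2);
- background incidence of neonatal stroke of 1 in 3,000 to 1 in 5,000 (Introduction).

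Input that is assumed: f, the share of symptomatic MRI-confirmed strokes with signs other than encephalopathy or seizures. The document does not give it; 10% to 30% is used for illustration.

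Formulas:
- births B = 200,000 × 0.95 × 6 = 1,140,000
- true cases c = B × true rate
- counted cases e = c × (1 − f)
- reported rate = e / B
- 95% interval for the count (Poisson, normal approximation) = e ± 1.96√e

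| True rate | f | True cases | Counted | Reported rate | 95% interval for the rate | True rate inside? |
|---|---|---|---|---|---|---|
| 1 in 3,000 | 10% | 380 | 342 | 1 in 3,333 | 1 in 3,014 to 1 in 3,728 | No, narrowly |
| 1 in 3,000 | 20% | 380 | 304 | 1 in 3,750 | 1 in 3,371 to 1 in 4,225 | No |
| 1 in 3,000 | 30% | 380 | 266 | 1 in 4,286 | 1 in 3,826 to 1 in 4,871 | No |
| 1 in 5,000 | 10% | 228 | 205 | 1 in 5,556 | 1 in 4,887 to 1 in 6,436 | Yes |
| 1 in 5,000 | 20% | 228 | 182 | 1 in 6,250 | 1 in 5,458 to 1 in 7,311 | No |
| 1 in 5,000 | 30% | 228 | 160 | 1 in 7,143 | 1 in 6,184 to 1 in 8,455 | No |

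The reported rate depends only on the true rate and f, for example 3,000 / 0.9 = 3,333 and 3,000 / 0.7 = 4,286. The number of births matters only for the intervals. If f is small, say 5%, the shortfall stays within sampling error: at 1 in 3,000 the reported rate is 1 in 3,158, with an interval of 1 in 2,863 to 1 in 3,521.

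**The case against.** The strongest case on the other side is that a registry may restrict itself to defined presentations, that the outcome is already called registry-based, and that the Introduction admits the estimate is not population surveillance and may be biased. This stands in part. The restriction is a legitimate design choice, but the caveat concerns the hospital base and referral, so a reader would not learn of the presentation filter from it.

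Several stronger readings are tempting, and the document does not support them:

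- **That only a single presentation is admitted.** Two are. Acute encephalopathy is also not defined, so a site might count apnoea or poor feeding under it. Only a case such as an alert infant with an isolated focal deficit clearly fails.
- **That silent infarctions are part of the undercount.** They are excluded openly and documented separately. They do not belong in f.
- **That MRI is required only after seizures.** The Discussion says that "the protocol mandates early cranial MRI and video EEG testing for infants presenting with postnatal seizures", but it does not say only, and 2.3.1 separately requires MRI screening of infants with identified risk factors.
- **That one undivided incidence is reported.** Section 2.7 stratifies it by gestational age, sex, birth weight and hospital level, and the Discussion plans subtype-specific analyses. What is absent is a breakdown by presentation or by what triggered imaging.
- **That the result cannot be compared with the earlier rates of 1 in 2,660 and 1 in 8,373.** The document does not give the presentation criteria of those studies, so this cannot be judged.

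It is also fair to say that 2.4.3 already has a module for clinical presentation and that the data form and dictionary are in supplements not shown. The module would describe enrolled infants, though; nothing in the article extends it to ineligible ones.

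**Conclusion.** The point holds as a mismatch between the eligibility rule and the named primary outcome. Followed as written, the plan measures the incidence of neonatal stroke presenting with acute encephalopathy or seizures, and reports it as the incidence of neonatal stroke. Symptomatic infants with other signs are provided for in neither the cohort nor the separate record.

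The bias is downward by the factor (1 − f). Its size cannot be fixed from the document. At an assumed f of 10% to 30%, a true 1 in 3,000 would be reported as 1 in 3,333 to 1 in 4,286. On about 1.14 million births, a share of roughly 10% (at 1 in 3,000) to somewhere between 10% and 20% (at 1 in 5,000) is enough to push the true rate outside the 95% interval. A broad local reading of encephalopathy would shrink f without bringing it to zero.

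A reader might infer that the primary result is invalid. The document does not support that: the size is unknown, the present count is meaningful once correctly named, and naming it correctly is within easy reach. Severity: moderate.

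**What to change.** 1. Keep the presentation criterion in 2.3.1 for the follow-up and prediction-model cohort.
2. In 2.1.1 and 2.5.1, name the present figure as the incidence of neonatal stroke presenting with acute encephalopathy or seizures.
3. Log every other symptomatic MRI-confirmed neonatal stroke diagnosed at the 22 hospitals, with a coded field for what triggered imaging (seizure, encephalopathy, other sign, risk-factor screening). Where consent is absent, keep a de-identified count if ethics approval allows.
4. Report the incidence of all diagnosed symptomatic stroke beside the restricted figure, over the same live births.
5. Leave silent infarctions in their separate record, as now planned.

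The cost is one coded field, one further incidence line, and an ethics question about counting infants without consent. The all-symptomatic figure will still depend on which infants are imaged, since the article states no imaging rule for infants with other signs and no identified risk factor. It should be labelled as an incidence of diagnosed stroke for that reason.

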#### Recruitment, screening, and informed consent

2.4.1

Neonates meeting the inclusion criteria will be prospectively identified and recruited by trained neonatologists from the NICUs and pediatric wards of the 22 participating hospitals. Two attending neonatologists at each site will be responsible for patient enrollment using standardized diagnostic criteria.

Written informed consent will be obtained from the parents or legal guardians after a definitive diagnosis is made. The study adheres to the ethical principles of the Declaration of Helsinki and has received institutional ethics approval.

To ensure rigorous standardization across the 22 participating centres, all enrolling neonatologists will undergo a mandatory centralized training workshop focused on standardized case definitions, MRI interpretation using a validated study atlas, and EEG acquisition protocols. In parallel, to maintain longitudinal data quality, annual inter-rater reliability assessments will be conducted using 10 blinded test cases. For diagnostic adjudication, all stroke subtypes will be centrally reviewed by an expert committee comprising three senior neonatologists and two neuroradiologists at Shenzhen Children's Hospital, who remain blinded to the initial site-level diagnosis. Furthermore, neuroimaging will adhere to a harmonized 3T MRI protocol (including DWI, SWI, and MRA/MRV sequences). Where 3T MRI is not immediately available at a participating center, arrangements will be made for patient transfer to a center with 3T capacity, and this will be documented. Specific scoring approaches for infarct volume (modified Pediatric ASPECTS) and PLIC assessment will be used centrally. All video-EEG recordings will be centrally interpreted by a single epileptologist masked to all clinical and imaging data.

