#### Secondary outcomes

2.5.2

Survival status at hospital discharge and throughout the 5-year follow-up period.Neurodevelopmental outcomes at 5 years were defined as a composite based on Bayley-4C scores and clinical diagnoses of impairments (e.g., cerebral palsy, epilepsy).Risk factor characterization (prenatal, perinatal, and postnatal).Performance of the developed prognostic prediction model for adverse neurodevelopmental outcomes.

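### MRI confirmation is a condition of entry, so stroke deaths before MRI count in the incidence denominator but cannot enter the numerator or the survival outcome; the effect is mainly on survival

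*Protocol article*

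**What the plan says.** Section 2.3.1 (Inclusion criteria) opens with "Participants must meet all the following criteria". One of these is "Neuroimaging confirmation (MRI) of stroke (arterial ischemic, hemorrhagic, or cerebral venous sinus thrombosis), excluding other common etiologies". The article gives no route to case status by CT, ultrasound or autopsy, and no category for probable or unconfirmed stroke.

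The safeguard for complete ascertainment in the same section is that neonates with risk factors "will undergo systematic screening with cranial MRI, and any asymptomatic infarctions detected will be documented separately". Section 2.4.1 adds "Where 3T MRI is not immediately available at a participating center, arrangements will be made for patient transfer to a center with 3T capacity", and on consent: "Written informed consent will be obtained from the parents or legal guardians after a definitive diagnosis is made".

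The incidence calculation is in the Introduction: "this registry enrols only diagnosed cases; therefore, cumulative incidence will be calculated using total live births from all 22 participating hospitals as the denominator". The Introduction then warns that "referral patterns may bias incidence estimates". Incidence is the primary outcome (section 2.5.1). Section 2.5.2 lists as a secondary outcome "Survival status at hospital discharge and throughout the 5-year follow-up period".

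**The concern.** Numerator and denominator follow different rules. Every live birth at the 22 hospitals counts in the denominator, whereas a stroke counts in the numerator only if the infant lived long enough, and became stable enough, to be scanned. Survival to MRI is thus a condition of entry, while survival to discharge is an outcome of the same cohort.

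The safeguard does not close this gap, because it is itself an MRI screen. Transfer to a 3T centre presupposes an infant who can be moved. The article provides for separate documentation of asymptomatic infarctions found on MRI, but describes no equivalent for infants who died or were never scanned. The biases it acknowledges are referral patterns (Introduction) and, among the limitations in the Discussion, attrition. Death before confirmation is not among them.

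There is also an internal tension. The definition of haemorrhagic stroke in section 2.4.4 names no imaging method, so a fatal haemorrhage seen only on ultrasound or CT could meet that definition and still fail section 2.3.1.

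At stake are a primary estimate that is too low and, more importantly, a survival estimate that is too favourable.

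**Working it through.** **Inputs from the article**
- Enrolment 300, mortality 10%, loss to follow-up 20%, outcome rate 30% (section 2.6).
- Background mortality 4% to 10%; neonatal stroke incidence roughly 1 in 3,000 to 1 in 5,000 (Introduction).

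**Input not in the article:** the number of stroke deaths before MRI. It is assumed below and varied.

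**Step 1: the plan's own figure.** 300 × (1 − 0.10 − 0.20) = 210 evaluable, as stated. 210 × 0.30 = 63 events, inside the stated 60 to 80. This point does not affect these figures. The planning figure for deaths is 300 × 0.10 = 30.

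**Step 2: direction.** Let m be true mortality and s the share of deaths that precede MRI. Then:
- observed incidence / true incidence = 1 − m·s
- observed mortality = m(1 − s) / (1 − m·s)

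Both fall below their true values whenever s > 0, so the direction needs no outside figure.

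**Step 3: size, starting from the planned cohort.** Take 300 enrolled with 30 deaths and add u missed cases, all fatal.

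| u | True mortality | Incidence understated by |
|---|---|---|
| 5 | 35/305 = 11.5% | 5/305 = 1.6% |
| 15 | 45/315 = 14.3% | 15/315 = 4.8% |

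These values of u correspond to s = 5/35 = 14% and 15/45 = 33%. Relative to the truth, mortality is understated by 1 − 10/11.5 ≈ 13% and 1 − 10/14.3 ≈ 30%. Survival would read 90% instead of 88.5% to 85.7%.

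**Step 4: size, starting from an assumed truth.**

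| True m | s | Observed / true incidence | Observed mortality |
|---|---|---|---|
| 10% | 10% | 99.0% | 9.1% |
| 10% | 25% | 97.5% | 7.7% |
| 10% | 50% | 95.0% | 5.3% |
| 4% | 10% | 99.6% | 3.6% |
| 4% | 25% | 99.0% | 3.0% |
| 4% | 50% | 98.0% | 2.0% |

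With m = 10%, a true 1 in 3,000 would read as 1 in 3,030 (s = 10%) to 1 in 3,158 (s = 50%).

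**Step 5: infants who are never scanned but do not die early.** Their omission lowers incidence. It biases mortality downwards only if they die more often than enrolled infants. For example, 10 missed infants with 10% mortality leave mortality unchanged, (30 + 1)/310 = 10%, while true incidence is 310/300 = 1.033 times the observed figure. An infant who is unstable at first but scanned later within the 28-day window can still enter and is not lost.

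**Step 6: comparison with sampling error.** For 300 cases the Poisson 95% half-width is about 1.96/√300 = 11%, well above 1.6% to 4.8%. For 30/300 the 95% Wilson interval is about 7.1% to 13.9%. The 11.5% lies inside it and the 14.3% just outside.

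**The case against.** The strongest reply is that this is a deliberate and partly disclosed definition. The outcome is called registry-based, and the Introduction says that only diagnosed cases are enrolled and that the cohort is hospital-based rather than true population surveillance. It also attributes the disagreement between earlier Chinese rates partly to differing imaging, so a uniform MRI definition is a reasonable response. This stands as a reason to keep MRI-confirmed stroke as the main figure. It does not answer the point, because neither the disclosure nor the limitations tell the reader that survival was measured only in infants who lived to be scanned.

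Second, the size is assumed and, for incidence, small beside sampling error. That stands. A reader might infer that the primary estimate is seriously distorted, and the figures do not support this. Nor is the 10% a forecast of mortality at discharge. It is an allowance for deaths before the five-year assessment, used here only as a scale.

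Third, a reader might infer that the losses concentrate in haemorrhagic stroke and shift the subtype mix, or that hospitals without on-site 3T lose more cases and so distort the stratification by hospital level. Both are plausible, but neither is shown. The article gives no mortality or time to death by subtype. The entry criterion says MRI rather than 3T, the Introduction states that cranial MRI is available at all participating hospitals, and nothing links 3T access to hospital level.

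Fourth, the article is condensed. The flow diagram and the data dictionary are not at hand, and a log of deaths or unscanned infants may exist there or in the full protocol. If it does, the fix is largely a matter of using it. The entry rule and the denominator, which create the bias, are both stated in the article.

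**Conclusion.** The point holds. Mandatory MRI confirmation, set against a denominator of all live births at the 22 hospitals, means that any stroke death before MRI lowers the observed incidence and raises the observed survival at discharge. The direction follows from the article's own definitions. The size does not: under the assumption of 5 to 15 missed deaths it is modest for the primary outcome and proportionally much larger for mortality. This should be corrected, mainly for the sake of the survival outcome, but it does not invalidate the design. The conclusion rests on at least some stroke deaths preceding MRI, and it needs no assumption about subtype or hospital level. The consent requirement and the exclusion for transfer or discharge before enrolment also reduce the numerator, but they are separate matters.

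**What to change.** - Keep MRI-confirmed stroke as the definition for the cohort, follow-up and modelling, and as the main incidence figure.
- Keep a case-level, de-identified log, subject to ethics cover, of neonates of eligible gestation who died or could not have MRI and who had stroke on CT, ultrasound or autopsy already done in care. Aggregate counts would not do, because they cannot be adjudicated.
- Have the existing central review committee (section 2.4.1) classify these infants as probable stroke.
- Report incidence and survival twice: for confirmed cases, and for confirmed plus probable cases.
- State in the limitations that survival to MRI is a condition of entry.

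The cost is a modest amount of extra review and less certain subtype classification in the probable group. Showing both sets of results lets the reader judge how much that matters. Enrolment was planned from January 2025 and early deaths become harder to reconstruct with time, so the log is best started soon. No new imaging and no change in care is proposed.
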